**Fig. 2 Fig2:**
[figure not shown]
Data collection.

### Adverse events

The allergy nurses will ensure that when performing skin prick testing, rescue medications are available at the time of the clinic in the unlikely event of a medical emergency. In the case of an adverse event, the allergy nurse has a responsibility to attend to the safety of the participant and report the incident as soon as is practicable to the on-call GP and practice manager and follow local reporting procedures within the practice. The allergy nurse will also keep a log of any adverse event or adverse reactions. Any serious adverse event or reactions will be reported immediately to the Academic and Clinical Central Office for Research and Development^17^ following the standard operating procedure.

### Outcome measures

This feasibility trial focuses on the ability to set up a new service in primary care, with a novel ‘hub and spoke’ referral model for patients with allergic disease. Prior to a pilot randomised controlled trial, it is important to assess the ability to recruit patients via this new service, and establish recruitment and retention rates and questionnaire response rates for future sample size estimates. The primary outcomes are:Recruitment of practices to facilitate establishing the new service and make referrals.Referral and consultation rates for nurse-led allergy clinic and retention rates.The change in disease-specific quality of life questionnaires between baseline and 6–12 weeks post intervention.

The following disease-specific quality of life questionnaires will be completed at baseline prior to the clinical intervention and at 6–12 weeks post intervention by telephone or email, and face to face for those patients who require a follow-up clinic appointment.Dermatology ○ Infants’ Dermatitis Quality Of Life Index^18^Allergic rhinitis○ Mini Rhinitis Quality of Life Questionnaire^19^Food allergy and anaphylaxis○ Food Allergy Quality of Life Questionnaire – Parent Form (children aged 0–12)^20^○ Food Allergy Quality of Life Questionnaire – Teenager Form (13–17 years)^21^○ Food Allergy Quality of Life Questionnaire – Adult form^22^

The secondary outcomes are:Patient satisfaction, measured immediately post intervention and 6–12 weeks post intervention by questionnaire.Referring HCP satisfaction measured after 1 year of the start of the nurse-led allergy clinics by questionnaire.Costs incurred by patients/carers.

A subset of referring HCPs, practice managers and patients/carers will be invited to take part in a semi-structured interview to gain in-depth insight into the feasibility of setting up and referring to the clinic, and to explore expectations and experiences of attending the nurse-led primary care allergy clinic.

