### Eligibility criteria

The inclusion criteria are:Children aged <36 months with suspected food allergy.Children aged <36 months with moderate-to-severe atopic eczema not responding to standard treatment.Children and young people up to 16 years of age with suspected allergic rhinitis symptoms are not responsive to a combination of oral antihistamines and nasal steroids.Young people and adults (from 16 years of age) with a history of anaphylaxis or suspected anaphylaxis.Able to give informed consent.

The exclusion criteria are:

Children aged <36 months with suspected or confirmed non-IgE-mediated food allergy presenting primarily with gastrointestinal symptoms.Single urticarial reactions without obvious triggers.Non-allergic chronic urticaria.Drug allergy.Well-controlled allergic rhinitis, asthma or atopic eczema.Mild-to-moderate atopic eczema without any obvious allergic trigger.Localised insect sting reactions.Unable to give informed consent.

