### The intervention

The intervention is a nurse-led allergy service in primary care. The nurses have a postgraduate qualification in allergy and extensive experience of secondary care allergy clinics and are supported when necessary by a team of specialist services, including paediatric and adult allergy, dermatology, ear, nose and throat, respiratory, and ophthalmology. Referring HCPs are asked to complete a referral proforma and a referral sheet for each eligible patient, which is sent via secure National Health Service (NHS) email to the allergy nurse. Referrals are triaged by the allergy nurse according to the inclusion/exclusion criteria, and allocated an appointment by phone and letter/email. The ~45-min appointment includes an explanation of the study, taking written consent, and completion of baseline questionnaires assessing disease-specific quality of life and costs incurred by the patients/carers (see outcome measures below). The nurse then completes an allergy-focused history and clinical examination. Following this, the nurse will carry out investigations such as skin prick testing, give advice (written and oral) to support the management of allergies, including demonstration of medical devices (e.g. adrenaline auto-injectors, inhalers) and, if required, recommend medication(s). A letter summarising the consultation is then sent to the referring HCP including details of the medication to prescribe and the rationale for prescribing these items. The participants are then discharged back to the care of their referring HCP once they have seen the allergy nurse and have a diagnosis confirmed or refuted (see Fig. 1).

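### Anaphylaxis from age 16 is eligible without restriction to food triggers, but the only quality-of-life forms assigned to it are food-allergy forms

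*Protocol article*

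**What the plan says.** The third primary outcome in the protocol article (Outcome measures) is "The change in disease-specific quality of life questionnaires between baseline and 6–12 weeks post intervention". The same section lists the questionnaires by condition:

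- one infant form for dermatology;
- one form, the "Mini Rhinitis Quality of Life Questionnaire", for allergic rhinitis;
- three food-allergy forms (parent 0–12, teenager 13–17, adult) under "Food allergy and anaphylaxis".

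The section also says that the trial should establish questionnaire response rates for use in later sample size estimates.

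The Eligibility criteria admit "Young people and adults (from 16 years of age) with a history of anaphylaxis or suspected anaphylaxis". The exclusions that bear on trigger are drug allergy and "Localised insect sting reactions". Rhinitis is admitted for "Children and young people up to 16 years of age with suspected allergic rhinitis symptoms", with no lower age.

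**The concern.** A disease-specific score has meaning only if the form concerns the respondent's disease. The anaphylaxis criterion is neutral as to trigger apart from the drug exclusion, while the forms that serve it are all about food. Someone referred after a systemic sting reaction would be asked before the consultation, and again at 6–12 weeks, about living with a food allergy.

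Two outputs are at stake. The quality-of-life change for this group would mix scores that describe the condition with scores that do not. The questionnaire response rate would mix willingness to respond with whether the form applied at all. Both feed the decision on a pilot randomised trial, so a planner could carry forward a change score or a response rate that partly reflects the wrong form.

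**Working it through.** The article gives no figure to reproduce on this point. The quality-of-life comparison is descriptive, and the target of about 250 with completed follow-up rests on time and resources and is not split by condition. The check is therefore a cross-match of each inclusion criterion (Eligibility criteria) with the form listed for it (Outcome measures).

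| Eligible group | Form listed | Match |
|---|---|---|
| Under 36 months, suspected food allergy | Food-allergy parent form, 0–12 | Yes |
| Under 36 months, moderate-to-severe eczema | Infant dermatitis form | Yes |
| Up to 16 years, suspected allergic rhinitis | One rhinitis form, no age range or parent version stated | Condition yes; age provision not stated |
| From 16 years, anaphylaxis, food trigger | Food-allergy teenager form (to 17) or adult form | Yes |
| From 16 years, anaphylaxis, non-food trigger | The same food-allergy forms | No |

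**Is the last row empty?** The drug-allergy exclusion removes one class of non-food trigger. The sting exclusion covers localised reactions only, so it leaves systemic sting reactions in. The row is narrowed but not emptied.

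**Where does it fall?** The food and eczema criteria stop at 36 months and the rhinitis criterion at 16 years. Anaphylaxis is the only criterion that admits people over 16. The adult quality-of-life summary therefore consists of anaphylaxis participants, and the form offered to them is the "Food Allergy Quality of Life Questionnaire – Adult form".

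**How large is the effect?** Let p be the share of the anaphylaxis group with a non-food trigger, d_F and d_N the mean change on the form in food and non-food cases, and r_F and r_N the response rates in each.

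- Reported mean change, if response is equal in the two: (1 − p)·d_F + p·d_N. This differs from the food-case value by p·(d_N − d_F).
- Reported response rate: (1 − p)·r_F + p·r_N. This differs from the food-case value by p·(r_N − r_F).

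The article gives none of p, d_F, d_N, r_F or r_N, so neither the size nor the direction of the distortion can be calculated.

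**The case against.** The strongest reply is that this is a single-arm feasibility study with no formal testing and no power claim. Finding out which questionnaires work is a proper feasibility result, referring condition will be described anyway, and the non-food group may be small. The full protocol or the data-collection figure, neither of which is shown, might say which form each participant receives. Much of this stands, and it limits the consequence. It does not remove the mismatch, because both lists are given in the article's text and, as printed, they do not fit together. Descriptive scores and response rates are also the trial's main output.

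A reader might infer more than the document supports:

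- **Rhinitis.** It is tempting to say that the rhinitis form is invalid in young children. That needs the form's validated age range, which the article does not give. Age-banded food forms do not prove the rhinitis form unsuitable. Only the absence of a stated age or parent provision can be shown.
- **Refuted allergy.** Participants leave the clinic once they "have a diagnosis confirmed or refuted", and one might conclude that refuted cases have no change score or become non-responders. They complete the form before the consultation, and nothing says that they skip the later one. Improvement after refutation may be a real benefit of the service.
- **Food-form ages.** The bands include ages 3 to 15, which no food or anaphylaxis criterion admits. The bands label the instruments, and a range wider than the recruited ages leaves nobody unmeasured.
- **A numerical dilution of the response rate.** This would need a true response rate and a share of inapplicable forms left blank. The article supplies neither.

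**Conclusion.** The point holds for non-food anaphylaxis from age 16. For these participants a primary outcome, and the response rate intended for planning, are taken from a form that does not fit the condition. This rests on three readings of the article: that the anaphylaxis criterion means what it says and is not silently limited to food, that the questionnaire list is complete, and that the forms concern food allergy, as their titles state. The number affected is unknown and may be small, but it falls within the only group that contains adults.

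The outcome as a whole is not compromised. Food allergy and eczema under 36 months, and food-triggered anaphylaxis, have matching forms. The rhinitis point is secondary: one form, a stratum reaching up to 16 with no lower age, and no stated provision for age or for completion by a parent.

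**What to change.** 1. State that the food-allergy forms are used only where food is the suspected trigger.
2. Classify non-food anaphylaxis as having no applicable form. Leave these participants out of the denominators for quality-of-life change and questionnaire response, and report how many there are. Keep them in recruitment and retention. The satisfaction questionnaire at 6–12 weeks still gives them a follow-up measure.
3. Report separately any food-form scores already collected from these participants, rather than discarding them or pooling them with food cases.
4. Report rhinitis scores by age. Do not switch instruments for participants who already have a baseline, because they would lose their change score and the stratum would be split across two forms.

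The cost is low. The Discussion section reports 214 patients already seen, and for them items 2 to 4 are a matter of classification and table layout, provided that the suspected trigger can be recovered from the referral or clinic record (an assumption, since the article does not say that it is recorded). The price is that fewer participants contribute to the adult quality-of-life summary.

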### Sample size

The sample size for this feasibility trial was informed by an English pilot study,^12^ which over a 9-month period recruited 141 patients to a primary care allergy clinic. We estimate that, taking account of the available time and resources for this study, ~250 patients with completed study follow-up will provide data to inform deliberations to proceed to a pilot randomised controlled trial.

We will interview up to ten HCPs/professional stakeholders, and 20 patients/carers who attend the nurse-led allergy clinic, to cover the experiences of patients and carers with a range of ages and allergic conditions.

### Descriptive analysis

We will describe the number of practices approached to act as hubs and spokes and the number recruited. The characteristics of referring practices in terms of number of patients referred, practice list size and deprivation score will be reported. For patients we will describe the number approached and recruited, age, sex and referring condition. We will report the retention rate for follow-up. For disease-specific quality of life, the difference in the disease-specific quality of life score at baseline and post intervention will be descriptively compared without any formal statistical testing. Patient and professional satisfaction with the service will be reported. Costs (such as travel and time off work) incurred by the patients/carers will be reported.

### Qualitative analysis

Interviews will be digitally recorded, transcribed verbatim and anonymised and transferred to NVivo (version 11) for coding. The thematic analysis^23^ will be iterative and ongoing, in that insights gained from the early interviews will be used to guide data generation in later interviews. The formal thematic coding will be framed around both the research questions and themes arising from the data. [name] will code all the transcripts and the evolving analysis will be reviewed by the study group at their quarterly meetings in order to include a range of interpretative perspectives.
